**Methods:**

This will be a group quasi-experimental trial with staggered cohort design. Data will be collected via direct measure and questionnaires at baseline, intervention completion (or waiting period for controls), and 10-weeks post-intervention. Setting will be faith-based community center. Participants will be 60 underserved families with at least 1, 4–10 year old child will be recruited and enrolled in the intervention (*n* = 30) or waitlist control group (*n* = 30). The intervention (Simple Suppers) is a 10-week family meals program designed for underserved families from racial/ethnic diverse backgrounds. The 10, 90-min program lessons will be delivered weekly over the dinner hour. Session components include: a) interactive group discussion of strategies to overcome family meal barriers, plus weekly goal setting for caregivers; b) engagement in age-appropriate food preparation activities for children; and c) group family meal for caregivers and children. Main outcome measures are change in: child diet quality; child standardized body mass index; and frequency of family meals. Regression models will be used to compare response variables results of intervention to control group, controlling for confounders. Analyses will account for clustering by family and cohort. Significance will be set at *p* < 0.05.

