**Table 1 Tab1:**
[figure not shown]
Simple Suppers Intervention Study Design: Two-Group, Staggered Cohort Quasi-Experimental Design

Following baseline data collection, families will decide whether to enroll in either the upcoming 10-week session of Simple Suppers (intervention group) or to wait for 10-weeks (waitlist control group) after which time they would begin the Simple Suppers program. Randomization of families is not feasible because of scheduling conflicts with participating families, the desire of families to participate in the program with families they know, and the need to establish trust with the site/participating families; thus, to preserve sample size and establish trust with the site/participating families, the personal preference of participating families will determine group membership.

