### Process measures

Feasibility (program dose and fidelity) and acceptability will be assessed prospectively throughout the study as process outcomes. Program dose will be assessed by collecting weekly attendance (family and individual level) and tracking presence of caregiver/child dyads at each weekly lesson. Participants who demonstrate irregular attendance and/or discontinue participation will be contacted to learn underlying reasons for absence. To determine program fidelity, a trained observer will complete a program specific fidelity tool at the end of each weekly lesson, which will include a checklist of key program components, activities, and leader characteristics. Acceptability of the program will be measured with a caregiver-completed 5-item satisfaction survey administered at the end of the 10-week program [41]. At the end of programming, interviews will be conducted with a subset of caregivers to learn their perceptions of program strengths and weaknesses.

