### Sample size and data analysis

Sample size was determined by examining the power of the test for comparing increases in frequency of family meals (day per week) of the intervention and waitlist control group. The data used to estimate power come from a previous pilot study, in which the main outcome of interest was the change in frequency of family dinners prepared and eaten at home together (weekly basis) from baseline to post-intervention [42]. Change in frequency of family dinners was used to power the current study because there is strong evidence that it has a downstream effect on the outcome of interest, child BMI [3, 42–44], and there are no previous studies that show a causal effect of family dinners on BMI. Based on these data, assuming 20% attrition [42], with an expected effect size of 0.7071, there will be 80% power to detect a difference in frequency of family dinners of 3 days per week with 30 families per group for a total sample size of 60 families at α = 0.05. Because the sample size in the previous pilot study was small and uncertainty about estimated effect size was large, we used a conservative estimate of effect size (i.e., the lower bound of a 95% confidence interval) for the power calculation.

Data from each of the three cohorts will be pooled and the intervention tested by comparing change (T1-T0) in diet quality, anthropometric measures, and blood pressure of child and caregiver participants in the intervention compared to participants in the waitlist control (hypotheses 1.1 and 2.1). Multiple regression models will be used to determine the association between the difference in the response variables of interest between the intervention and control group, controlling for potential confounders (race/ethnicity, income, cohort, intervention dose), from baseline (T0) to 10-week post-test(T1) and 10-week follow-up (T2). For families in which data will be collected on multiple children, the effect of family will also be controlled by including a random effect for family.

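### Adjusting the intervention-versus-waitlist models for lesson attendance changes the estimand and can remove part or all of the programme effect

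*Protocol article*

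**What the plan says.** Sample size and data analysis in the protocol article sets out the main test: three cohorts are pooled and "the intervention tested by comparing change (T1-T0) in diet quality, anthropometric measures, and blood pressure" between intervention and waitlist participants, for hypotheses 1.1 and 2.1. Multiple regression is then to estimate "the association between the difference in the response variables of interest between the intervention and control group". The article gives the adjustment set for these models as follows: "controlling for potential confounders (race/ethnicity, income, cohort, intervention dose"). The models cover change from T0 to T1 and to T2, with a random effect for family where several children are measured.

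Process measures says what dose is: "Program dose will be assessed by collecting weekly attendance (family and individual level"). The same section gives it a different role: "Feasibility (program dose and fidelity) and acceptability will be assessed prospectively throughout the study as process outcomes".

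Study design says that families choose either to start the coming session or "to wait for 10-weeks (waitlist control group) after which time they would begin the Simple Suppers program". The Abstract gives the maximum exposure: "The 10, 90-min program lessons will be delivered weekly over the dinner hour".

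**The concern.** A confounder precedes, or at least does not result from, the choice of group. Race/ethnicity, income and cohort meet that description. Attendance does not: it is recorded after the family has joined a group, the group determines whether it can be above zero at all, and the lessons are how the programme reaches families. The article itself calls the same quantity a process outcome in one section and a confounder in another.

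The comparison at stake is the main one. With attendance held fixed in the T0 to T1 model, the group coefficient no longer answers whether families offered the programme improved more than families who waited. A programme that works could show a small or very uncertain group effect.

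**Working it through.** **Inputs from the article.** Standardised effect d = 0.7071, stated for family dinners; 30 families per group; 20% attrition, so 30 × 0.8 = 24 per group; α = 0.05, sidedness not stated; at most 10 lessons. Waitlist dose of 0 at T1 is inferred from the 10-week wait.

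**Assumed.** Mean m and SD s of lessons attended in the intervention group, since the article gives neither.

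**The plan's own figure.** The article says "with an expected effect size of 0.7071, there will be 80% power". By the normal approximation, power = Φ(d√(n/2) − z):
- one-sided, n = 24: Φ(2.449 − 1.645) = 78.9%
- two-sided, n = 30: Φ(2.739 − 1.960) = 78.2%
- two-sided, n = 24: Φ(2.449 − 1.960) = 68.8%

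The 80% is therefore approximately reproduced with a one-sided test, or with a two-sided test that ignores attrition. It is not in dispute here and serves only as a benchmark.

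**What the group coefficient becomes at T1.** Write change = a + b·group + c·dose + error, with dose = 0 in every waitlist family. The control mean fixes a, and c is estimated only within the intervention group. If Δ is the difference in group means, then Δ = b + c·m, so

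b = Δ − c·m.

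This is the intervention line read at zero lessons, minus the control mean. Three cases with Δ = 0.7071:
- Benefit proportional to attendance: c = Δ/m, so b = 0.
- Half the benefit through attendance: c = Δ/(2m), so b = 0.35.
- Benefit unrelated to attendance: c = 0, so b = 0.71.

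**What happens to its standard error.** With residual variance σ² and n per group,

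Var(b) = σ²(1/n + 1/n + m²/(n·s²)) = (2σ²/n)·(1 + m²/(2s²)).

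Without dose the variance is 2σ²/n, so the standard error is multiplied by √(1 + m²/(2s²)). The last column gives two-sided power (normal approximation, both tails) at 24 per group when benefit is unrelated to attendance, against 68.8% without dose.

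| Assumed attendance | m²/(2s²) | SE multiplier | Power with dose in the model |
|---|---|---|---|
| mean 5, SD 3 | 25/18 = 1.39 | 1.5 | 35% |
| mean 7, SD 2 | 49/8 = 6.13 | 2.7 | 15% |
| mean 9, SD 1 | 81/2 = 40.5 | 6.4 | 7% |

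For the middle row: 2.449/2.669 = 0.918, and Φ(0.918 − 1.960) + Φ(−0.918 − 1.960) ≈ 15%. The penalty is worst when attendance is high and uniform, that is, when the programme is best delivered.

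**Simulation check.** There were 6,000 trials per case, with attendance drawn from a normal distribution with mean 7 and SD 2, rounded and limited to 0–10, and two-sided tests.

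| Case | Per group | Coefficient without → with dose | Power without → with dose |
|---|---|---|---|
| Proportional | 30 | 0.69 → −0.01 | 74% → 5% |
| Half | 30 | 0.70 → 0.35 | 76% → 8% |
| Unrelated | 30 | 0.71 → 0.69 | 77% → 15% |
| Proportional | 24 | 0.70 → −0.01 | 66% → 5% |
| Half | 24 | 0.70 → 0.35 | 66% → 7% |
| Unrelated | 24 | 0.71 → 0.72 | 67% → 13% |

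The simulated standard error rose about 2.9-fold, slightly above the formula's 2.7, because the cap at ten lessons narrows the spread of attendance and the spread varies between samples.

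**The case against.** The best defence has four parts.

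*Coding.* If dose were centred at the intervention-group mean, with controls set to 0, it would be uncorrelated with group and the coefficient would equal the plain difference in means. That is correct algebra. Nothing in the article points to such coding, though, and a variable coded so as to leave the group effect untouched is not being used to control confounding.

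*Intent.* The authors may have meant a dose-response analysis. The article describes none; it places dose in the between-group model. This is a stated rule, not a detail left to a fuller document.

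*No randomisation.* Families choose their group, so adjustment is needed. For baseline differences it is, and the Discussion plans for that. Attendance is not a baseline variable, and because it is self-selected, conditioning on it may add bias.

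*Strength and reach.* A reader might infer that the adjustment always removes the effect, that every control has zero dose throughout, and that dose must leave every between-group model. The article supports none of these.
- Full removal requires benefit proportional to attendance; the 5% power in that case follows from the assumption and does not predict this trial's result.
- Zero dose among controls holds only to T1. By T2 the waitlist families have had the programme, so the standard-error formula above does not carry over.
- The replication comparison (waitlist T2−T1 against intervention T1−T0) has both groups receiving the programme and is outside this point.

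These limits stand. They narrow the claim but leave the T0 to T1 problem in place.

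**Conclusion.** The covariate list is wrong as written for the intervention-versus-waitlist regressions. For hypotheses 1.1 and 2.1 at T1, dose as an ordinary covariate turns the group coefficient into a contrast at zero lessons attended. How much of the effect is lost depends on how far benefit runs through attendance: all of it, part of it, or none but at a price in precision. That price is a standard error about 1.5 to 6.4 times larger over the attendance patterns tried.

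At T2 control dose is no longer zero and these figures do not apply, but dose is still measured after baseline and is still part of treatment.

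The conclusion rests on zero waitlist dose at T1, inferred from the design, and on dose entering as an uncentred count. The sizes rest on assumed attendance and, for power, on the family-dinner effect size; the article states no effect size for the hypothesis 1.1 outcomes. Calling the last case unbiased also assumes that attendance is not related to change for other reasons, and it means unbiased relative to the model without dose, which is itself not protected by randomisation.

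**What to change.** In Sample size and data analysis, delete intervention dose from the covariates of the intervention-versus-waitlist models, for T1 and T2. Keep baseline covariates only: race/ethnicity, income, cohort, and any baseline differences adjusted for under the Discussion. The family random effect is unaffected. State that the effect is estimated by the group each family chose, regardless of lessons attended. Report the relation between attendance and change among programme participants as a separate analysis labelled exploratory.

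The cost is one phrase deleted and one analysis relabelled. Attendance is still collected as a process measure, and neither data collection nor sample size changes.

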### Study design

The study will be implemented over 12-months as a two-group (intervention; waitlist control) quasi-experimental trial using a staggered cohort design (Table 1). At each of three time periods, separated by 10 weeks, a cohort of 20 families will be recruited. Each cohort will be divided into an intervention and waitlist control group (10 families in each). Consequently, a total of 60 families (30 in the intervention group and 30 in the waitlist control group) will be enrolled. Upon confirmation of study eligibility, a baseline data collection appointment will be scheduled at the participating family’s home or the community center during the two weeks preceding intervention commencement. Data will be collected on the primary food preparing caregiver and all children 4–10 years old. Written caregiver consent and child assent will be obtained. Data will be collected on all outcomes via direct measure and questionnaires at baseline (time point 0, T0), 10-week post-test (time point 1, T1), and 10-week follow-up (time point 2, T2). Repeatability of the intervention (replication) will be evaluated by assessing measures on the waitlist control group at T1 and T2. Assessments will last up to 90 min. A team of trained research staff, blinded from group assignment, will facilitate data collection. Caregiver participants will receive a $25 grocery store gift card at each data collection point for their participation in the research. All study materials and procedures have been approved by the Institutional Review Board at Ohio State University.

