Sustainability of intervention effects will be tested by pooling intervention group data from each of the three cohorts, comparing change (T2-T1) in diet quality, anthropometric measures, and blood pressure among intervention group participants at the end of the 10-week follow-up period (hypothesis 1.2 and 2.2). Intervention replication will be assessed by pooling waitlist control group data from each of the three cohorts, comparing post-program change in diet quality, anthropometric measures, and blood pressure among waitlist control participants (T2-T1) to intervention participants (T1-T0). Significance will be set at *p* < 0.05.

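### The intervention-versus-control regression is also run to T2, when the waitlist families have had the programme, so its T0-T2 contrast compares early with delayed programme

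*Protocol article*

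**What the plan says.** All references are to the protocol article.

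- **Regression (Sample size and data analysis).** Multiple regression is to address "the difference in the response variables of interest between the intervention and control group", adjusted for race/ethnicity, income, cohort and intervention dose, "from baseline (T0) to 10-week post-test(T1) and 10-week follow-up (T2").
- **Timing of the waitlist programme (Study design, text after Table 1).** Families who choose the waitlist are "to wait for 10-weeks (waitlist control group) after which time they would begin the Simple Suppers program".
- **Programme length (Abstract, Methods).** "The 10, 90-min program lessons will be delivered weekly over the dinner hour".
- **Assessments (Study design).** Baseline is T0, followed by "10-week post-test (time point 1, T1), and 10-week follow-up (time point 2, T2").
- **Role of the waitlist T1 and T2 data (Study design).** "Repeatability of the intervention (replication) will be evaluated by assessing measures on the waitlist control group at T1 and T2".
- **Replication analysis (Sample size and data analysis, last paragraph).** It works by "comparing post-program change in diet quality, anthropometric measures, and blood pressure among waitlist control participants (T2-T1) to intervention participants (T1-T0").
- **Maintenance analysis (same paragraph).** It uses the T2-T1 change "among intervention group participants at the end of the 10-week follow-up period (hypothesis 1.2 and 2.2").

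The test of hypotheses 1.1 and 2.1 is tied to the T1-T0 change.

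**The concern.** The same waitlist T2 measurements have two incompatible roles. The replication analysis treats them as measurements taken after the programme. The regression sentence, on its plain reading, treats them as control data. Only the first role fits the design.

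A T2 result reported as intervention versus control, at the article's p<0.05 threshold, invites the wrong reading. A programme that works in both groups and lasts would give a T2 difference near zero. A programme that works in both groups and partly fades would give a difference favouring control. Either could be reported as a lost or harmful effect although every family had benefited.

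**Working it through.** **Step 1. Exposure at each assessment.** The table follows the prose; the content of Table 1 was not legible in the text reviewed.

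| Assessment | Intervention group | Waitlist group |
|---|---|---|
| T0 | not yet exposed | not yet exposed |
| T1 | end of programme | not yet exposed (end of waiting period) |
| T2 | 10 weeks after programme | end of programme |

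T1-T0 compares programme with no programme. T2-T0 compares two groups that have both had it.

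**Step 2. Does any hypothesis need T2-T0 between groups?** No. Hypotheses 1.1 and 2.1 use T1-T0. Hypotheses 1.2 and 2.2 use T2-T1 within the intervention group. Replication compares the waitlist T2-T1 change with the intervention T1-T0 change.

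**Step 3. Do the covariates repair it?** No. Intervention dose is the exposure itself, and by T2 both groups have been offered the lessons. Adjusting for it does not restore an untreated comparator.

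**Step 4. The article's own power figure, for scale.** Inputs from Sample size and data analysis: effect size 0.7071, a difference of 3 dinners per week, 30 families per group, 20% attrition, alpha 0.05, stated power 80%. Completers: 30 x 0.80 = 24 per group. Normal approximation: power = Phi(d / sqrt(2/n) - 1.96).

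- n = 30: 0.7071 / sqrt(2/30) = 2.739, power 78.2% (t-test 76.8%).
- n = 24: 0.7071 / sqrt(2/24) = 2.449, power 68.8% (t-test 66.9%).

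The stated 80% is roughly matched two-sided if attrition is ignored, or one-sided with 24 completers (78.9%). Nothing below depends on which was meant.

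**Step 5. Expected T0-T2 contrast.** Let m be the share of the effect that intervention families keep at T2, and r the share that waitlist families gain from their own programme. Positive values favour the intervention group.

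Expected contrast = (m - r) x 0.7071 SD = (m - r) x 3 dinners per week.

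The article gives neither m nor r; both are assumptions. The rates below also assume that the T0-T2 change has the same SD as the T0-T1 change, and that there is no baseline difference or covariate effect. They are two-sided t-test rates at alpha 0.05, with r = 1 (full replication).

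| m | Expected contrast (SD) | Dinners/week | p<0.05, n = 24 | p<0.05, n = 30 |
|---|---|---|---|---|
| 1 | 0 | 0 | 5% | 5% |
| 0.75 | -0.177 | -0.75 | 9.2% | 10.3% |
| 0.5 | -0.354 | -1.5 | 22.4% | 27.0% |
| 0 | -0.707 | -3.0 | 66.9% | 76.8% |

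The normal approximation gives 23.2% and 27.8% in the m = 0.5 row. In that row nearly all significant results favour the waitlist group; the opposite tail is below 0.1%.

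**Step 6. Varying replication.** Only m - r matters. With m = r = 0.5, half the effect is present in both groups and the contrast is again 0. With m = 1 and r = 0.5 it is +0.354 SD, half the true effect in the intervention group. It equals the maintained effect only when r = 0, that is, when the waitlist programme does nothing.

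**The case against.** Three counter-arguments carry weight.

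- **No hypothesis depends on this contrast.** This is correct. The efficacy test is T1-T0, maintenance is assessed within the intervention group, and the article calls the waitlist T2-T1 change post-programme, so its authors know that the controls are treated by T2. This limits the damage but does not make the T2 group contrast interpretable.
- **The sentence is loosely worded.** It defines no T2-T0 change score. It might only name the data waves, or describe a repeated-measures model whose T2 coding sits in a fuller plan that is not shown. That is possible. But the sentence is about a difference between intervention and control and lists T2 without qualification, so the plain reading includes the contrast. If it was not intended, the text should say so.
- **The size is hypothetical.** The -0.35 SD and the 22% rest on an assumed half retention and full replication. The zero under full maintenance and full replication rests on the outcome the protocol itself hopes for.

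A reader might infer that the T0-T2 comparison cannot show any effect, or that the trial's main conclusion is compromised. The documents support neither. Early versus delayed programme can be estimated, and it can differ from zero if the effect decays or grows, or if the self-selected groups respond differently. The main test compares with an untreated group at T1.

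**Conclusion.** The point holds for one sentence of the analysis section. Followed as written, it yields a T2 estimate labelled intervention versus control that has no untreated comparator and cannot estimate programme versus no programme. Its timing basis is explicit in the article and needs no assumption. The size does: zero requires equal effects in the two groups at T2, and -0.35 SD with about 22% significant results requires half retention, full replication, the 0.7071 SD design effect for family dinners and 24 completers per group. No effect size is given for diet quality, BMI z-score or the other outcomes, so the figures are not carried over to them. The direction of the problem applies to every outcome in the regression. The T1-T0 test and the maintenance and replication analyses stand.

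**What to change.** Restrict the between-group regression to the T0-T1 change. Use T2 only for the two analyses already planned: T2-T1 within the intervention group for maintenance, and waitlist T2-T1 against intervention T1-T0 for replication. If a T0-T2 group contrast is kept, label it early versus delayed programme and state that it will not be interpreted as an intervention effect or as loss of effect. The cost is a change of wording, with no new data or visits.

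Optionally, add one longitudinal model over T0, T1 and T2 with time-varying exposure (not yet exposed, end of programme, 10 weeks after). The waitlist T0 and T1 measures must be coded as unexposed and only their T2 measure as end of programme; coding T1 as exposed would remove the untreated comparator from the main test. The model needs calendar-period and shared-effect assumptions, and the latter presupposes the replication that the trial sets out to assess. With family random effects it also draws on between-family differences, so families' choice of group can still bias it.

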## Methods

### Objectives and hypotheses

The objectives of this study with related hypotheses will be as follows:Assess the impact of Simple Suppers on children and caregivers of participating families relative to children and caregivers of families in the control group.Hypothesis 1.1.Diet quality, BMI z-scores and BMI, waist circumference (WC) z-scores and WC, and BP z-scores and BP will improve more from baseline to post-intervention among children and caregivers, respectively, participating in the intervention than in the controls.Hypothesis 1.2.Diet quality, BMI z-scores and BMI, WC z-scores and WC, and BP z-scores and BP improvements will be maintained during the follow-up period among children and caregivers, respectively, participating in the intervention.

Objective 2.Assess the impact of Simple Suppers on the family meals environment of participating families relative to the controls.Hypothesis 2.1.Frequency of family meals (breakfast and dinner), TV viewing during meals, and eating family meals in a dining area will improve more from baseline to post-intervention among families participating in the intervention than in the controls.Hypothesis 2.2.Frequency of family meals (breakfast and dinner), TV viewing during the meals, and eating family meals in a dining area improvements will be maintained during the follow-up period among families participating in the intervention.

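### Hypotheses 1.2 and 2.2 say improvements are maintained, but the stated test (T2-T1 change within the intervention group at p < 0.05) can show further change and cannot support maintenance

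*Protocol article*

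**What the plan says.** Under Objectives and hypotheses, hypothesis 1.2 states that diet quality, anthropometric and blood pressure "improvements will be maintained during the follow-up period among children and caregivers, respectively, participating in the intervention". Hypothesis 2.2 makes the parallel statement for family meal frequency, television viewing during meals and eating in a dining area.

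The last paragraph of Sample size and data analysis names the test for both hypotheses. Intervention group data are pooled over cohorts, and the analysis consists of "comparing change (T2-T1) in diet quality, anthropometric measures, and blood pressure among intervention group participants at the end of the 10-week follow-up period". The same paragraph handles replication by "comparing post-program change in diet quality, anthropometric measures, and blood pressure among waitlist control participants (T2-T1) to intervention participants (T1-T0"), and it closes with the only criterion given: "Significance will be set at *p* < 0.05". Study design describes replication in different terms: "Repeatability of the intervention (replication) will be evaluated by assessing measures on the waitlist control group at T1 and T2".

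The power statement covers something else, the between-group comparison of dinner frequency. It says that "there will be 80% power to detect a difference in frequency of family dinners of 3 days per week". Its inputs are a standardised effect of 0.7071, alpha 0.05, 20% attrition and two groups of 30.

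**The concern.** Maintenance is a claim that no important loss occurred. The named contrast is a test of difference, whose null hypothesis is no change from T1 to T2. Rejecting that null shows that something changed. Not rejecting it shows only that the data were too imprecise to detect a change, or that there was none. Neither result establishes maintenance.

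The contrast also starts at T1. An outcome that never improved between T0 and T1 and then stayed flat gives T2-T1 = 0, the same result as a gain fully kept.

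At stake is the conclusion on two listed hypotheses. If a non-significant result were reported as maintenance, the claim would become easier to make as families drop out.

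**Working it through.** **Inputs from the article (Sample size and data analysis).** Standardised effect 0.7071 for the between-group change in dinner frequency; 30 families per group; 20% attrition, so 30 × 0.8 = 24 completers; alpha 0.05, sidedness not stated; power 80%.

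**The plan's own figure.** With n per group = 2((z_alpha + z_0.80)/d)² and d² = 0.5:
- One-sided: 4 × (1.645 + 0.842)² = 24.7, so 25 completers per group, and 25/0.8 = 31.25, so 32 enrolled. Power with 24 per group is 0.79.
- Two-sided: 4 × (1.960 + 0.842)² = 31.4, so 32 completers per group, and 32/0.8 = 40 enrolled. Power is 0.69 with 24 per group and 0.78 with 30.

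So 30 per group is about right if the test is one-sided after attrition, or two-sided with attrition ignored. Both sample sizes and both forms of the test are therefore used below.

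**Assumptions for the illustration.** The article gives no within-group gain and no SD for T2-T1. I take 0.7071 SD as the gain at T1, an SD of T2-T1 change of 1, and one unit per family.

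**Maintenance.** The test is a one-sample t-test on T2-T1 with noncentrality δ√n, where δ is the loss in SD units. For loss of half the gain, δ = 0.3536:
- n = 24: noncentrality 0.3536 × √24 = 1.73, against a two-sided critical value of 2.07.
- n = 30: noncentrality 0.3536 × √30 = 1.94, against 2.05.

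| True loss | 24 families, two-sided | 30 families, two-sided |
|---|---|---|
| Quarter of gain (0.177 SD) | 87% non-significant | 85% |
| Half (0.354 SD) | 62% | 53% |
| Three quarters (0.530 SD) | 30% | 20% |
| All (0.707 SD) | 9% | 4% |

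Further results with 24 families:
- A one-sided test (critical value 1.71) leaves loss of half the gain non-significant 49% of the time.
- The two-sided test reaches 80% power at a loss of 0.60 SD, which is 0.597/0.7071 = 84% of the assumed gain.
- If the SD of T2-T1 is 0.7 or 1.2 instead of 1, the 62% becomes 34% or 72%.
- If the gain is only 0.3 SD, noncentrality for its complete loss is 0.3 × √24 = 1.47, and the loss is missed 71% of the time. At 0.5 SD it is missed 35% of the time.

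**Replication, if judged by a two-sample difference test.** Noncentrality is δ√(n/2). With a waitlist response half the size of the intervention group's and n = 24 per group, it is 0.3536 × √12 = 1.22 against 2.01, so the difference is non-significant 78% of the time (73% with 30). With no waitlist response at all, it is non-significant 33% of the time (23% with 30).

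**A margin-based claim.** Take a margin of half the gain (0.354 SD, an assumption), one-sided alpha 0.025 and no true loss. Power is Φ(0.3536√n − 1.96). With 24 families this is Φ(1.73 − 1.96) = 41%; with 30 it is 49%. For 80% power, n = ((1.960 + 0.842)/0.3536)² = 62.8, so 63 completers, and 63/0.8 = 78.75, so 79 enrolled.

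**The case against.** A reader might infer that the plan counts p > 0.05 as maintained or replicated. It does not say so. It says only which changes will be compared and at what significance level, so that reading is an inference. It remains the only route by which the named contrast could support hypotheses 1.2 and 2.2.

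Replication is on softer ground. It is not among the listed hypotheses, the comparison may be meant descriptively, and the Study design wording allows a test within the waitlist group from T1 to T2, where a significant improvement would be the success. The 78% applies to one reading only.

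A reader might also infer that follow-up is never related to baseline. In fact the regression paragraph covers change from T0 to both T1 and T2, and hypothesis 1.1 tests whether there was an improvement at all. That softens the point about T0. It does not supply a test of maintenance: by T2 the waitlist group has been through the programme, so there is no untreated comparator, and the article assigns 1.2 and 2.2 to the T2-T1 contrast.

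The figures borrow a between-group effect on dinner frequency for within-group changes in other outcomes, which have no stated effect size. Several children per family would also add correlated units. This objection stands, so the figures are illustrations.

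Finally, margins and interval reporting are often left to an analysis plan. The absence of a margin is therefore not the complaint. The complaint is that the contrast and threshold which the article does fix do not match the hypothesis they are assigned to.

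**Conclusion.** The concern holds for maintenance. The test assigned to hypotheses 1.2 and 2.2 can demonstrate further change but not that a gain was kept. Under the stated assumptions, loss of half the gain would go undetected in roughly half to three fifths of trials (49% to 62% across the one- and two-sided tests with 24 families and the two-sided test with 30). Complete loss of a gain as large as 0.7071 SD would usually be detected, so the weakness lies in partial loss and in smaller gains.

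For replication the point is a caution only. The documents do not support saying that the plan declares maintenance or replication from a non-significant p. The main between-group comparison at T1 is not affected.

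**What to change.** For hypotheses 1.2 and 2.2, report the intervention group's T2-T0 and T2-T1 changes with 95% confidence intervals. Claim maintenance only if the T1 effect was shown and the T2-T1 interval excludes a loss larger than a share of the gain stated in advance. If no margin is set, report the estimates and draw no maintenance claim from p > 0.05.

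For replication, report the waitlist group's T2-T1 change against its own T1-T0 change, and its difference from the intervention group's T1-T0 change, each with a confidence interval. Do not infer replication from a non-significant difference.

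The cost is wording and, if a claim is wanted, one pre-stated margin; no new data are needed. The downside is that the claim becomes hard to make: about 41% power with 24 families at a half-gain margin, even with no true loss. Estimation without a claim is the likely result.
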